**FIGURE 1 F1:**
[figure not shown]
Motivation barometer.

#### Additional Content and Resources

Additional resources were developed to complement the workshops in each condition and to improve participant adherence.

##### Control condition

A list of websites is available on the final slide of the workshop and an A4 hard copy of the list is distributed to participants. The list signposts the WADA website, the relevant NADO website, how to check for banned substances in medication, and the process of reducing the risk of inadvertent doping through supplement use. In addition, coaches are provided with information on how they can report any suspicions of doping to the relevant authorities. A hard copy of the slides is also provided to coaches.

##### Experimental condition

The coaches in this condition receive the same information as those in the control condition. In addition, A5 workbooks are provided which include (**Figure 2**):

**FIGURE 2 F2:**
[figure not shown]
Workbook examples.

•Content from the presentation slides with questions to check understanding and summaries of main points.•Descriptions of the practical activities run in the workshops.•A personal action plan for coaches to implement the motivational strategies taught in the workshops. We created action and coping planning sheets for coaches to think through how/when strategies might be used, what challenges they might face in doing so, and how these challenges can be overcome.•Instructions on a week-by-week basis regarding the practicalities of implementing motivational strategies when communicating with athletes. Detailed descriptions are given on how to implement these strategies before, during, or after training. Coaches can keep a reflective diary of success and failures in implementing in their coaching sessions what they have learned at the workshops.

The workbooks are designed to be portable to allow coaches to carry them during training sessions and to take notes. The coaches are encouraged to utilize the workbooks throughout the program.

The project teams have also created restricted access Facebook groups for participating coaches in the experimental condition in each country. The Facebook groups provide coaches with the opportunity to engage in discussions with the project team and interact with fellow coaches participating in the program. For coaches not on Facebook, they receive a weekly email communication from the project team. The team provides weekly prompts via Facebook or email to remind coaches to continue to implement the strategies taught during the workshops, as outlined in their workbooks. In addition, the groups are used to disseminate topical information, including research publications, news articles, and videos illustrating different motivational strategies/communication styles by coaches. We have also created videos with amateur actors depicting different styles of coach communication. These video clips are designed to assist the coaches to grasp the motivational concepts discussed during the workshops. The coach actors in the video clips reinforce to the athlete actors the importance of providing accurate information about the risks of supplement use. However, different video clips have been created (each about 5 min long) in which a coach is interacting with an athlete in need supportive, need thwarting, or motivationally neutral ways.

### Piloting of the Material

Pilot deliveries of the intervention workshops have been conducted across all three countries using between 5 and 7 coaches of varying experience. Following the workshops, coaches were invited to provide feedback via evaluation questionnaires. During these workshops, coaches were able to provide comments on the general workshop approach/delivery in addition to the specific interactive activities and material that we prepared. The feedback has been very positive and will be presented in a future process evaluation publication.

### Phase 2

In this phase, we are currently delivering a cluster randomized control trial in Australia, United Kingdom, and Greece. This study is a parallel group, two-condition, superiority trial. Due to calendar differences in the start of sport seasons, the intervention started half a year earlier in Australia than in the other two countries. Recruitment is ongoing in Greece and the United Kingdom and has been completed in Australia, hence the description of the methodology in this section is written in future tense.

#### Participants and Recruitment

We will recruit from sport clubs 20 full-time or part-time coaches in each condition from each country, giving a total sample size of 120 coaches and estimated 1200 athletes. There are no exclusion criteria for coaches based on their own demographic or coach history characteristics. Inclusion criteria include having a minimum of six athletes who are 14 years or older, train at least once a week, and compete on a regular basis. No more than six coaches will be recruited from any given club, and coaches within that club will be allocated to the same condition. Due to the number of recruited participants, we will use a staggered recruitment design. We will aim to recruit from a variety of sports in all three countries, and from both male and female coach and athlete samples. Power estimates have been calculated with the Optimal Design Software (Spybrook et al., 2011) for clustered RCTs with treatment at level 2, primary outcomes at level 1, estimated average number of athletes per coach to be 10, intraclass correlation coefficient of 0.005, small effect size (δ =0.22) for willing to engage in doping, and oversampling by about 30% to counter possible missing values and coach/athlete dropout from the study. Clubs will be assigned randomly to either a control or intervention condition with a 1:1 allocation using permuted blocks of random sizes. The block sizes will not be disclosed to ensure concealment. A researcher will carry out randomization (and allocate clubs to the two arms) via a computer software following recruitment. Allocation concealment will be ensured, as randomization will not be disclosed until after the intervention starts. All research assistants who will collect data will be blind to condition allocation. There will be no circumstances in which unblinding for those individuals will be necessary. Due to the nature of the intervention, participants cannot be blinded to allocation, but they will be strongly encouraged not to discuss the content of their training with coaches from other sport clubs until after the end of the program.

Recruitment will be carried out by the research team who will liaise with sport governing bodies, coach organizations, and sport clubs in and around Perth (Australia), Thessaloniki (Greece), and Leeds (United Kingdom). Forms of recruitment will include face-to-face contact (e.g., meetings with club president or providing an information session to coaches), flyers, information delivered via email, and promotion via social media (e.g., twitter) with links to the project’s website (e.g., for the Australian website^3^).

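### The power calculation treats the coach as the randomised cluster although clubs are randomised, so it overstates power by an amount the protocol does not let one fix

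*Protocol article*

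**What the plan says.** Everything needed is in one paragraph of the protocol article, Participants and Recruitment (Phase 2).

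- **Randomisation.** "Clubs will be assigned randomly to either a control or intervention condition with a 1:1 allocation using permuted blocks of random sizes".
- **Coaches within clubs.** "No more than six coaches will be recruited from any given club, and coaches within that club will be allocated to the same condition".
- **Power calculation.** It is described as being for "clustered RCTs with treatment at level 2, primary outcomes at level 1, estimated average number of athletes per coach to be 10", with an "intraclass correlation coefficient of 0.005" and a "small effect size (δ =0.22) for willing to engage in doping". About 30% is added for missing values and dropout. The result is 120 coaches and an estimated 1200 athletes.

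The paragraph gives no alpha, no target power, no number of clubs, no average number of coaches per club and no club-level ICC. The Analyses section describes the nesting as athletes within coaches and does not name the club, so nothing elsewhere in the article shows that the club level entered the calculation.

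**The concern.** With outcomes on athletes at level 1 and cluster size counted per coach, level 2 is the coach. Treatment at level 2 then means that each coach is allocated independently. The trial does not do this: all coaches of a club go to the same arm, so the independent units are clubs, and a club can hold up to 6 × 10 = 60 athletes. The cap of six and the same-arm rule show that clubs with several coaches were expected.

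Two things reduce power when the club is the randomised unit. Athletes of different coaches in one club may be correlated, which the calculation takes as zero. The treatment contrast also has fewer degrees of freedom, because clubs rather than coaches are counted. At stake is the justification of the sample size for the primary outcome, willingness to take potentially illegal substances. If the real power for 0.22 is lower than believed, a null result could be read as excluding that effect more firmly than it should.

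**Working it through.** **Inputs from the protocol article:** effect δ = 0.22; m = 10 athletes per coach; ICC = 0.005; 120 coaches; about 30% oversampling; 1:1 allocation of clubs; at most 6 coaches per club.

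**Assumed, because not stated:** two-sided 5% test; 92 analysed coaches (120/1.3 = 92.3); k coaches in every club; the ICCs at each level. Fractional numbers of clubs are kept.

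**Step 1. The plan's own design, coach as cluster.** With J coaches, the variance of the treatment contrast is 4 × [ICC + (1 − ICC)/m]/J. Power comes from a noncentral t with J − 2 degrees of freedom.

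For J = 92: 4 × (0.005 + 0.0995)/92 = 0.00454, noncentrality 0.22/√0.00454 = 3.26, power 89.8%. For J = 120, power is 95.9%.

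**Step 2. Can the 120 be reproduced?** Coaches needed under coach-level randomisation:

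| Target power | Coaches | × 1.3 | ÷ 0.7 |
|---|---|---|---|
| 80% | 70 | 91 | 100 |
| 85% | 80 | 104 | 115 |
| 90% | 93 | 121 | 133 |
| 95% | 115 | 150 | 165 |

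The closest match is 90% power with × 1.3. This is a back-fit, not a figure the article states.

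**Step 3. Club as the randomised unit.** With K = J/k clubs, the variance is 4 × [ICC_club + ICC_coach/k + (1 − ICC_club − ICC_coach)/(km)]/K, with K − 2 degrees of freedom. Placing the whole stated 0.005 at club level, with J = 92:

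- k = 2: 4 × (0.005 + 0.995/20)/46 = 0.00476; noncentrality 3.19; 44 df; power 87.7%.
- k = 3: 4 × (0.005 + 0.995/30)/30.67 = 0.00498; noncentrality 3.12; 28.7 df; power 85.4%.
- k = 6: 4 × (0.005 + 0.995/60)/15.33 = 0.00563; noncentrality 2.93; 13.3 df; power 77.5%.

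With one coach per club the result equals step 1 and there is no loss.

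**Step 4. Other cases.** Power for δ = 0.22:

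| Coaches analysed | ICC club / coach | k = 2 | k = 3 | k = 6 |
|---|---|---|---|---|
| 120 | 0.005 / 0 | 94.7% | 93.4% | 88.6% |
| 92 | 0.0025 / 0.0025 | 88.4% | 86.9% | 81.5% |
| 92 | 0.005 / 0 | 87.7% | 85.4% | 77.5% |
| 84 (30% lost) | 0.005 / 0 | 84.4% | 81.8% | 73.0% |
| 92 | 0.005 / 0.005 | 86.3% | 84.0% | 76.1% |
| 92 | 0.01 / 0.01 | 82.2% | 78.3% | 66.5% |
| 92 | 0.02 / 0.02 | 74.3% | 68.1% | 52.2% |

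The first four rows keep the total ICC at the article's 0.005. The last three use totals of 0.01, 0.02 and 0.04, which are two, four and eight times that value.

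**Step 5. Detectable effect.** With 92 coaches and 0.005 at club level, the effect detectable with 90% power is about 0.23, 0.24 and 0.26 for k = 2, 3 and 6. With 80% power it is about 0.20, 0.20 and 0.23.

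**The case against.** The strongest reply is that the mismatch is small on the article's own figures and that its size is unknown.

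- **No target power is stated.** The 90% is inferred, so nobody can say that a promised power is missed. This stands.
- **Six is a ceiling, not an average.** With 2 or 3 coaches per club and the stated ICC, the loss is about 2 to 4 percentage points. With one coach per club there is none. This stands.
- **Full retention would leave ample power.** With all 120 coaches and 0.005 at club level, power is at least 88.6%. This stands, although the article itself plans for losses of about 30%.
- **The analysis may gain precision.** It is longitudinal with a baseline measurement, which the post-only formula above ignores. This is possible, but the article does not quantify it.

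A reader might go further and infer that 120 can be obtained only if coaches were randomised separately. The arithmetic does not support that. At 92 coaches with 0.005 at club level, power is 85.4% with 3 per club and 80.3% with 5 per club, and 92 × 1.3 = 119.6. Likewise 84 coaches with 0.005 at both levels and 3 per club give 80.3%, and 84/0.7 = 120. So the match to 120 says nothing about which design was used. The mismatch rests on the wording of the calculation.

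A reader might also take the figures of 52% or 68% as the trial's real power. They depend on ICCs well above the only one in the article.

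None of this removes the error: the article says which level carried treatment in the calculation, and that is not the level it randomises.

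**Conclusion.** The sample-size justification uses a cluster that is not the randomised unit. The direction is clear: with more than one coach in some clubs and a club ICC above zero, power for 0.22 is overstated.

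The size is not determined. On a two-sided 5% test with 92 analysed coaches, about 90% becomes about 88%, 85% or 78% for 2, 3 or 6 coaches per club when the stated 0.005 sits at club level. If all 120 coaches are retained, about 96% becomes about 95%, 93% or 89%. A serious shortfall needs club sizes near the ceiling or ICCs several times the stated value, for example 68% and 52% for 3 and 6 per club with 0.02 at each level.

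The documents do not support the conclusion that 120 coaches are too few. They support the conclusion that the stated calculation does not show they are enough. This is a should-fix point.

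**What to change.** Redo the calculation as a three-level design (athletes, coaches, clubs) with treatment at club level.

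- State the number of clubs and the average coaches per club. Recruitment in Australia was already complete when the article was written, so observed figures were partly available.
- Give separate ICCs for club and coach, with a short range for the club value.
- State alpha, sidedness and the form of the 30% inflation.
- Report the resulting power for 0.22, or the detectable effect at a named power, for 120 coaches.

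The cost is a recalculation and probably a somewhat less favourable stated figure. No change to enrolment is required.

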### Procedure

**Table 1** demonstrates an overview of the process involved for coach and athlete participation for each condition. In summary, the intervention period starts in week 1 and ends in week 12. Coaches and athletes in each condition provide measures prior to week 1. Then, coaches in the intervention condition will receive the first workshop in week 1 and the second workshop in week 5. Coaches in the control condition receive their workshop in week 1. Coaches in the intervention condition are given weekly tasks each week up to week 12. The weekly tasks in the first 4 weeks focus on planning activities that aim to increase the use of need supportive communication and avoid or minimize the use of need thwarting behaviors when coaches are interacting with their athletes. The weekly tasks in weeks 5–12 focus on planning activities that aim to help coaches to initiate discussions about doping issues using a need supportive communication style. As explained earlier, coaches are assisted in these weekly activities via a number of resources available in their workbooks and via the private Facebook group. Coaches and athletes in both arms provide assessments after the intervention, that is, in week 13, as well as 2 months later. The coaches in the control condition will receive the motivational workshop (and all associated resources) after all assessments have been completed. However, due to resource constraints, they will not have the ongoing support from us should they wish to put in practice what they have learned.

**Table 1 T1:** The SPIRIT schedule of enrolment, interventions, and assessments.

[figure not shown]

To promote participant retention, athletes will be entered into a prize draw to win monetary retail vouchers if they complete all assessments. In order to promote retention of coaches in the trial, the research team will be in regular contact with them throughout the intervention period via phone and email. There will be no other data collected from athletes or coaches if they refuse to continue participation in the study. All coaches will receive a certificate from the research team and a monetary retail voucher if they complete all aspects of the project.

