In this last phase of the project, we will implement a thorough process evaluation of the intervention via coach and athlete interviews, coach questionnaires on ease and usefulness of the training material, as well as fidelity to the protocol assessments. We plan to interview either individually or in a group format between 5 and 10 coaches and athletes in each country from the experimental condition. The purpose of the interviews with the coaches will be to ascertain their views on the training they received and its different components (e.g., workshops, online material). We will establish which components the coaches liked or disliked (and why), and how often they engaged with those components in their coaching practice. We will also discuss successes and challenges the coaches experienced in integrating the training material in their coaching practice. Suggestions will also be sought from the coaches in terms of material modification and, more generally, in terms of program modification. This qualitative information will be combined with quantitative ratings that coaches (from both arms) will provide at the end of each workshop and at the end of the study. These ratings will provide evaluations of the perceived usefulness and clarity of the different components of the training and the coaches’ efficacy in utilizing those. The interviews with athletes will establish whether the athletes noticed any changes in their coaches’ communication (in terms of content and style) about (anti)doping from before to after the program.

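### The request not to share training content with other clubs appears to end with the 12-week training, about 9 weeks before the 2-month follow-up

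*Protocol article*

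**What the plan says.** Participants and Recruitment states that participants cannot be blinded. It then strongly encourages them "not to discuss the content of their training with coaches from other sport clubs until after the end of the program". No calendar date or assessment is attached to that end point.

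The Procedure section sets the timetable: "the intervention period starts in week 1 and ends in week 12". On outcomes it says: "Coaches and athletes in both arms provide assessments after the intervention, that is, in week 13, as well as 2 months later". On the control arm it says: "The coaches in the control condition will receive the motivational workshop (and all associated resources) after all assessments have been completed".

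On entry to the trial, Participants and Recruitment says that "we will use a staggered recruitment design". Clubs come from one area per country (Perth, Thessaloniki, Leeds). The spacing of waves within a country is not given. The Phase 3 process interviews are planned with "coaches and athletes in each country from the experimental condition".

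**The concern.** The design means control coaches to stay unexposed to the motivational content through the last assessment, because it holds back the workshop and its resources until then. The request not to share content is tied to a different milestone, the end of the program. If that is the end of training, intervention coaches may talk freely to control coaches in the same area while control outcomes are still to be collected.

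Sharing would move control coaches' behaviour towards the intervention and shrink the difference between arms. The Analyses section plans a longitudinal multilevel model, so the follow-up data enter the main analysis. A smaller difference at 2 months could then reflect a fading effect, control uptake, or both.

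**Working it through.** **1. What program means in the article.**

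| Place | Use of the word |
|---|---|
| Objectives | The intervention training and the control training are each a program; the whole undertaking is the project |
| Additional Content and Resources, experimental condition | The period over which coaches use their workbooks |
| Phase 3 | Athletes are asked about change in their coach from before to after it |
| Procedure | Weeks 1 to 12 are called the intervention period; the voucher for full participation is tied to the project |
| Conclusion | The trial itself is described as an anti-doping education program |

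The first three uses point to the coach training and the last to the whole trial. The training is the usual meaning, but the word is never defined.

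**2. The uncovered window.** Inputs from Procedure: training ends in week 12; assessments fall in week 13 and 2 months later. Two months is taken as 8 to 8.7 weeks.

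- Last assessment: 13 + 8 = week 21, to 13 + 8.7 = week 21.7.
- Weeks after the request ends: 21 − 12 = 9, to 21.7 − 12 = 9.7.
- Share of time on study: 9/21 = 43%, to 9.7/21.7 = 45%.

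If program means the whole trial, the window is 0 weeks. For clubs that start together, only the step from week 12 to week 13 precedes the post-intervention assessment, so that comparison is essentially covered on either reading.

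**3. What dilution would do (illustration only).** The plan's sample size is reproduced first. Inputs from Participants and Recruitment: n = 10 athletes per coach, ICC ρ = 0.005, δ = 0.22, about 30% oversampling, 120 coaches. Assumed, because not stated: two-sided alpha 0.05.

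- Variance of the difference with J coaches = 4[ρ + (1 − ρ)/n]/J = 4(0.005 + 0.0995)/J = 0.418/J.
- With the noncentral t on J − 2 degrees of freedom, 90% power needs J = 93, and 93 × 1.3 = 120.9, close to the stated 120. At 80% power J = 70, and 70 × 1.3 = 91, which does not match. The plan's figure therefore fits an assumed 90% power.

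Now suppose that a share c of control athletes have a coach who takes up the material with full effect. The difference becomes 0.22 × (1 − c). Power is shown for all 120 coaches and for 92 (120/1.3 = 92.3):

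| c | Difference | Power, 120 coaches | Power, 92 coaches |
|---|---|---|---|
| 0 | 0.220 | 95.9% | 89.8% |
| 10% | 0.198 | 91.4% | 82.8% |
| 20% | 0.176 | 84.1% | 73.3% |
| 30% | 0.154 | 73.5% | 61.8% |

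The document gives no value for c. Full uptake from informal talk is a generous assumption, since the intervention is two 3-hour workshops with weekly supported tasks.

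**The case against.** The best defence is that program may mean the trial. The Conclusion uses it that way, and the authors had another term, intervention period, for weeks 1 to 12. The request also goes to all participants. Control coaches have only a 1-hour workshop in week 1, so a single trial-wide end point would suit both arms. The exact instruction may sit in the presenters' slide notes, which are not shown. This stands as far as it goes: the lapse at week 12 is the natural reading, not a stated fact. It does not settle the matter, because the published wording can be read either way and three country teams must apply it.

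A reader might infer several stronger points that the document does not support:

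- **That the control arm is left unprotected.** Clubs are randomised whole, the Facebook groups are restricted to experimental-arm coaches, and control coaches do not get the materials. None of this ends at week 12. The request is an additional, non-binding measure.
- **That contamination is not looked for at all, or that a fading effect could never be told from control uptake.** Athletes in both arms rate need-supportive and need-thwarting coach behaviour at all three time points, and the Hypotheses call this the manipulation check. Rising need support in the control arm would suggest uptake; falling need support in the intervention arm would suggest fading. Role plays are compared between arms, but only before and after the intervention. These measures could show a shift but not its source, and no direct question on exposure is described.
- **That later clubs are exposed during their own weeks 1 to 12.** This needs overlapping waves within one area. Staggering is stated and spacing is not. The only documented offset, half a year, is between Australia and the other two countries.
- **That the effect would fall to any particular value.** The dilution figures above rest on assumed shares.

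**Conclusion.** The point holds in a limited form. On the usual meaning of program in the article, the request ends about 9 to 9.7 weeks before the last outcome, while the same article keeps the content from control coaches until all assessments are complete. The exposure is mainly at the 2-month follow-up, and possibly earlier for later-recruited clubs if waves overlap. Any bias would run towards no effect. Its size cannot be derived from the document, and 43 to 45% measures time outside the request, not bias.

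The conclusion rests on reading program as the training; on the trial-wide reading there is no gap and only the wording needs clarifying. It does not rest on wave overlap, because the follow-up gap exists even if all clubs start together.

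**What to change.** Replace the end point of the request with: *until the last participating club in that country has completed its 2-month follow-up*. State it to both arms. Ask control coaches who receive the delayed motivational workshop before that date to follow the same request.

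Optionally, add one item to the control coaches' week-13 and follow-up packs asking whether they have seen or discussed the other arm's material. Report the share who had, and read it alongside the athlete-rated need-support manipulation check.

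The cost is one changed sentence, one optional item, and a longer period in which coaches are asked to hold back content. No extra participants are needed. Recruitment was still open in Greece and the United Kingdom when the article was written, so the wording could be set there for clubs yet to enter; coaches already trained would need a reminder.
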